## Eligibility criteria (inclusions/exclusions)

### Inclusion criteria

Aged between 18 and 75 years (inclusive) at time of screeningAetiology: One or more of:Alcohol-related liver disease (no active alcohol misuse ≥6 calendar months prior to screening). Features of chronic liver disease with a compatible history of alcohol excess (>80 g/day), in the absence of other causes of chronic liver disease.PBC 2 out of: Cholestatic liver function tests (LFTs), Positive antimitochondrial antibody (titre >1:40). Compatible liver histology (if already receiving ursodeoxycholic acid must be established on current dose >3 months prior to enrolment).NAFLD Either: Histological evidence of hepatic steatosis in the absence of other liver diseases Or: Imaging compatible with NAFLD (eg, fatty infiltration of liver) and one or more risk factors (eg, elevated body mass index, type 2 diabetes mellitus, hypertriglyceridaemia, hypertension) and the absence of significant alcohol consumption (<20 g/day) and no evidence of other causes of chronic liver disease.Cryptogenic cirrhosis diagnosis of cirrhosis unattributable to any other cause.Haemochromatosis diagnosis made on basis of compatible biochemistry (transferrin saturation >60%, ferritin >400), genotype (homozygous C282Y or H63D compound heterozygote) or histology.Alpha-1 antitrypsin deficiency diagnosis based on compatible genetic, phenotypic or histological testing.Previous chronic hepatitis C (sustained viral response ie, undetectable HCV RNA 24 weeks after treatment).Diagnosis of cirrhosis—invasive or non-invasive criteria cirrhosis defined as any of:Biopsy-confirmed diagnosis of cirrhosis.Transient elastography (TE)—≥15 kPa.Clinical and radiological features which in the opinion of the investigator correlate with a diagnosis of cirrhosis.A MELD score (Pre-2016) of ≥10 and ≤17 at screening visit.

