#### Allocation

Participants will be assigned to receive either standard medical care or to receive a fresh dose of autologous MDMs at the maximum achievable dose, in a 1:1 ratio based on a minimisation algorithm using the key variable aetiology of disease (ALD, NAFLD, other.) To ensure the allocation is random, participants will be assigned to the group which minimises the imbalance with probability 0.8. If a participant falls into two or more strata, then the dominant aetiology (as determined by treating physician) will be used.

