### Statistical analysis plan

The baseline to 90-day change in MELD score will be compared in the two treatment arms using a two-sample t-test or non-parametric equivalent as appropriate. MELD scores calculated for each participant throughout the trial will be used to calculate an area under the curve (AUC) and this will be compared across the groups using a two-sample t-test or non-parametric equivalent as appropriate. In the event of varying durations in the trial follow-up, the average AUC per month will be used so that all participants have a comparable measurement.

Changes in secondary outcome measures (ELF score liver stiffness, CLDQ score, transplant-free survival, number of clinical events, UKELD score, blood parameters (bilirubin, albumin, ALT, INR)) over the 1-year study period will be presented graphically by dose. Similarly, these results will used to calculate an AUC for each participant and will be compared across the groups using a two-sample t-test or non-parametric equivalent as appropriate.

The only planned subgroup analysis is to present the primary outcome by disease aetiology (ALD, NAFLD, other). Primary data analysis will be conducted on participants who receive a single infusion versus control; the primary analysis will then be repeated to include those subjects who receive more than one infusion (three individuals). There are no plans for an interim analysis.

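### The primary MELD change and the AUCs are compared without adjustment for baseline or the minimisation factor: a valid analysis, but less efficient than one using data already collected

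*Protocol article*

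**What the plan says.** Under Statistical analysis plan, the protocol article sets out the primary comparison, which concerns movement in MELD from baseline to day 90: "change in MELD score will be compared in the two treatment arms using a two-sample t-test or non-parametric equivalent as appropriate". MELD scores from the whole of follow-up are then "used to calculate an area under the curve (AUC) and this will be compared across the groups using a two-sample t-test" or its rank-based counterpart. For the secondary measures the article will "calculate an AUC for each participant and will be compared across the groups using a two-sample t-test or non-parametric equivalent as appropriate". No covariate is named for any of these comparisons.

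Under Allocation, participants are assigned in a "1:1 ratio based on a minimisation algorithm using the key variable aetiology of disease", in three classes (ALD, NAFLD, other), with probability 0.8 of going to the arm that reduces imbalance. In the analysis section aetiology returns only as the single planned subgroup presentation of the primary outcome.

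Eligibility requires a MELD score "of ≥10 and ≤17 at screening visit". Table 1 shows MELD measured at visits 1a and 1b, before any treatment. MELD is not a minimisation factor.

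**The concern.** Two items known before treatment could sharpen the comparison: the baseline value of the outcome and the factor on which allocation is balanced. The plan uses the first only by subtraction in the primary outcome, and the second not at all as an adjustment.

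- **Baseline MELD.** A change score gives baseline a fixed slope of 1. Where the true slope is lower, the estimate carries avoidable noise.
- **Aetiology.** Balancing a prognostic factor by design reduces the real variability of the treatment difference. The ordinary two-sample standard error does not reflect that, so intervals are wider than they need be.
- **MELD AUC.** It is computed from the scores themselves, so baseline is not removed. A chance difference in baseline MELD between two small arms goes directly into the AUC difference.

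With 23 evaluable participants planned per arm, and a stated aim of informing later trial design, the width of the intervals matters.

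**Working it through.** **1. The plan's own figure.** Inputs (Sample size/power calculation; Interventions): difference 1 SD of the change score, two-sided 5%, 90% power, 23 per group, 5 dropouts per arm. The normal approximation n = 2(1.960 + 1.282)² / 1² = 21.0 rounds up to 22. The exact t solution is 22.02, which rounds up to 23. Power at 23 per arm is 91.2%, and 23 + 5 = 28. The stated size reproduces.

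**2. Baseline adjustment of the primary outcome.** The document gives no baseline to day-90 correlation ρ, so a range is assumed, with equal variances σ² at the two times.

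- Variance of the change score: 2σ²(1 − ρ).
- Residual variance after ANCOVA: σ²(1 − ρ²).
- Ratio: (1 + ρ)/2.

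| ρ (assumed) | Variance ratio | Power at 23 per arm, formula only | Power, simulated with baseline and aetiology in the model |
|---|---|---|---|
| 0.5 | 0.75 | 96.9% | 96.6% |
| 0.7 | 0.85 | 94.9% | 94.3% |
| 0.8 | 0.90 | 93.8% | 92.6% |
| 0.9 | 0.95 | 92.5% | 91.6% |

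The comparator is about 91% unadjusted. The formula column ignores the degrees of freedom spent on covariates; the last column allows for them and is the one to use. For an effect of 0.5 SD, the formula takes power from 38% to 48%, 44% and 40% at ρ = 0.5, 0.7 and 0.9.

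Leaving baseline out as a covariate does not disturb the size of the change-score t-test: simulated type I error at ρ = 0.5, 0.7 and 0.9 was 4.9%, 5.1% and 5.0%.

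**3. Omitting the minimisation factor.** The stated scheme (one three-level factor, probability 0.8) was simulated with 20,000 trials per setting. R² is the share of variance in the analysed outcome that aetiology explains; it is not given and is assumed. Entries are the type I error of the unadjusted t-test at nominal 5%.

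| Total N, aetiology mix | R² = 0 | 0.05 | 0.10 | 0.20 | Adjusted test |
|---|---|---|---|---|---|
| 46, equal | 4.9% | 4.6% | 4.1% | 3.1% | 5.0% |
| 46, 50/30/20 | 5.3% | 4.8% | 4.2% | 3.2% | 5.3% |
| 56, equal | 5.1% | 4.6% | 4.0% | 2.9% | 5.1% |
| 56, 50/30/20 | 4.8% | 4.3% | 3.9% | 3.0% | 4.8% |

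In round terms this is 5%, 4.5%, 4% and 3%. The adjusted test stays near 5% throughout. Power for 1 SD at N = 46 (equal mix), unadjusted against adjusted for aetiology alone, is 92.4% against 93.8% at R² = 0.10, and 93.3% against 96.0% at R² = 0.20.

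**4. MELD AUC.** If r is the correlation between baseline MELD and the AUC, adjustment leaves 1 − r² of the variance: 0.75, 0.51, 0.36 and 0.19 at r = 0.5, 0.7, 0.8 and 0.9. This r is not the ρ of step 2, and the document gives neither.

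**The case against.** The strongest defence is that the plan is coherent. The trial is sized for a two-sample test on the change score, the sample size reproduces under that test, and the target power is met. Nothing inflates false positives. All of this stands, and it limits the point to efficiency and calibration.

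The size of the gain is also uncertain. No correlation or R² is given. At ρ = 0.9 the gain in power for 1 SD is under one percentage point, and if day-90 MELD varies more than baseline it shrinks further. Subtracting baseline already removes stable differences in MELD level between aetiologies, so aetiology may explain little of the 90-day change; at R² = 0 the conservatism vanishes. This too stands.

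A reader might infer more than the document supports:

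- That the primary test ignores baseline MELD. It does not; the change score subtracts it.
- That both omissions make the p-values conservative. Only the omission of aetiology can, and only if aetiology is prognostic.
- That every AUC is of raw values. The sentence on secondary measures opens with changes in those measures and then builds the AUC from these results, which may mean changes. Only the MELD AUC is plainly of raw scores.
- That baseline MELD spans 10 to 17. That is the screening criterion; MELD is measured again at visit 1b.
- That the choice between t-test and rank test is left to be made on the data. The article gives no rule, but such a rule is commonly left to a full analysis plan, which is not shown.

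**Conclusion.** The point holds as a recommendation on efficiency. The article positively specifies unadjusted comparisons, so this is a stated choice and not a detail left open. The choice is valid but does not follow the allocation scheme or make full use of baseline.

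For the primary outcome the cost ranges from about six percentage points of power (ρ = 0.5) to under one (ρ = 0.9) for a 1 SD effect, and it matters more for smaller effects. The conservatism from omitting aetiology ranges from none to a type I error of about 3%, according to an R² that is unknown. The MELD AUC is where baseline is handled least well, because it is not removed at all; the gain there could be large but depends on an unknown correlation. The sample size and the control of false positives are not in question.

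**What to change.** Make the primary analysis an ANCOVA of day-90 MELD on randomised arm, baseline MELD and aetiology (ALD, NAFLD, other), and report the adjusted difference with its 95% confidence interval. Analyse the MELD AUC, and the AUCs of the continuous secondary measures (ELF, liver stiffness, CLDQ, UKELD and the blood parameters), with each measure's own baseline and aetiology as covariates. Keep the unadjusted two-sample test as a named sensitivity analysis.

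The cost is a change of wording in the analysis plan and three degrees of freedom: one for baseline and two for aetiology. Table 1 schedules a baseline for each of these measures, and aetiology is entered at randomisation, so no new data are needed and the sample size does not change.

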##### Non-invasive markers of fibrosis

Changes in our secondary outcome measures over 90 days up to maximal 360 days as per schedule (table 1), these include: serum enhanced liver fibrosis (ELF) test (iQur, London, UK, serum Protein Fingerprint markers (Nordic Bioscience, Herlev, Denmark), hepatic TE (Echosens, Paris, France) and the UK End-Stage Liver Disease (UKELD) score.

**Table 1 T1:** Trial assessment schedule

	Visit 1a	Visit 1b	Treatment group				Control group					
			Visit 2a Within 7±4 days of Visit 1b	Visit 2b 7>10 days after apheresis (Day 0)	Visit 2c (Day 7)	Visit 2d (Day 14)	Visit 2 (day 7±4 days from visit 1b)	Visit 3 (Day 28*±4* days)	Visit 4 (Day 56*±4* days)	Visit 5 (Day 90*±7* days)	Visit 6 (Day 180*±7* days)	Visit 7 (Day 360*±7* days)
Informed consent	X											
Clinical assessment	X	X	X	X	X	X	X	X	X	X	X	X
Vital signs	X	X	X	X	X	X		X	X	X	X	X
Screening blood tests	X											
ECG	X											
Standard blood tests	X	X		X	X	X		X	X	X	X	X
Research bloods*			X		X	X	X	X	X	X	X	X
Mandatory microbiology	X		X									
Ferritin	X			X†	X	X						
Triglyceride	X			X†	X	X						
Pre-infusion blood tests				X								
MELD/UKELD	X	X		X	X	X		X	X	X	X	X
Pregnancy test	X‡	X‡		X‡	X§							X‡
Abdominal Ultrasound Scan (USS)	X¶										X¶	X¶
Fibroscan	X									X	X	X
ELF panel	X							X	X	X	X	X
Protein fingerprint	X¶							X¶		X¶		
CLDQ		X								X	X	X
31P MRS MRI**	X*									X		
Adverse events	X	X	X	X	X	X	X	X	X	X	X	X
Clinical events	X	X	X	X	X	X	X	X	X	X	X	X
Concomitant Medication	X	X	X	X	X	X	X	X	X	X	X	X

*If pass screen and before visit 2b.

†Obtain before discharge.

‡women of child bearing age only.

§If test not carried out at previous visit.

¶Fasted visit.

**Royal Infirmary of Edinburgh (RIE) patients only.

CLDQ, Chronic Liver Disease Quality of Life Questionnaire; ELF, enhanced liver fibrosis; MELD, Model for End-Stage Liver Disease; MRS, MR spectroscopy; UKELD, UK Model for End-Stage Liver Disease.

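### The MELD, UKELD and blood-test AUCs rest on different visit grids in the two arms, because only the macrophage arm is sampled between Visit 1b and day 28

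*Protocol article*

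**What the plan says.** In the Statistical analysis plan section, the rule for the MELD AUC is "MELD scores calculated for each participant throughout the trial will be used to calculate an area under the curve (AUC". No restriction to particular visits follows. The secondary measures, among them "UKELD score, blood parameters (bilirubin, albumin, ALT, INR)) over the 1-year study period", are treated alike: "Similarly, these results will used to calculate an AUC for each participant and will be compared across the groups". The one provision for comparability concerns length of follow-up: "In the event of varying durations in the trial follow-up, the average AUC per month will be used so that all participants have a comparable" (the sentence closes just after this).

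Table 1 (under Non-invasive markers of fibrosis) gives the sampling times. The MELD/UKELD row and the standard blood test row have the same pattern. Both are marked at Visits 1a and 1b, then in the treatment columns at Visit 2b, headed "Visit 2b 7>10 days after apheresis (Day 0", and at Visits 2c (day 7) and 2d (day 14). The only control visit in that interval, headed "Visit 2 (day 7±4 days from visit 1b", is blank in both rows. The marks resume at Visits 3 to 7 (days 28, 56, 90, 180 and 360). The column headings of the table are flattened in the text. I read Visits 3 to 7 as common to both arms, since the day-90 primary outcome needs both.

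**The concern.** An AUC built from every available score depends on when scores are taken. Here the timing depends on the allocated arm. In the treated arm the curve between baseline and day 28 passes through measured values at days 0, 7 and 14. In the control arm it is a straight line from Visit 1b to day 28. If patients in both arms have a short rise or dip in those weeks that has gone by day 28, the treated AUC includes it and the control AUC cannot. The comparison then shows a between-arm difference, in either direction, that the treatment did not cause. Dividing by months of follow-up leaves this untouched.

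At stake are the supportive AUC tests for MELD, UKELD, bilirubin, albumin, ALT and INR. The primary comparison uses baseline and day 90 only. ELF, liver stiffness and CLDQ have the same scheduled visits in both arms.

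**Working it through.** The plan gives no figure for the AUC analysis. Its nearest figure, 23 per group, belongs to the primary outcome. It reproduces (the two-sample t-test solution for 1 SD, two-sided 5%, 90% power is 22.02, rounded up to 23) and serves below only as the arm size.

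**Assumptions not in the documents.** The AUC is trapezoidal. A transient excursion of d points is present at the early visits and gone by day 28.

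**Weights with day 0 as origin and a baseline value at day 0 in both arms.** Each visit's weight is half the sum of the gaps on either side.
- Macrophage arm (days 0, 7, 14, 28, 56, 90, 180, 360): 3.5, 7, 10.5, 21, 31, 62, 135, 90 days.
- Control arm (days 0, 28, 56, 90, 180, 360): 14, 28, 31, 62, 135, 90 days.

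Both sum to 360. If the course is linear from baseline to day 28, the two AUCs agree exactly.

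**Excursion at days 7 and 14 only.** The treated AUC gains 7d + 10.5d = 17.5d point-days and the control AUC gains 0. On the time average this is 17.5/360 = 0.049d for follow-up to day 360, and 17.5/90 = 0.194d for follow-up to day 90.

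**Excursion at days 0, 7 and 14, with Visit 1b as origin.** Table 1 puts Visit 2a 3 to 11 days after Visit 1b. Taking apheresis to be at Visit 2a and the infusion 7 to 10 days later, Visit 1b lies L = 3 + 7 = 10 to 11 + 10 = 21 days before day 0. The added area is (L/2 + 7 + 7 + 14/2)d.
- L = 10: 26d. Time average 26/370 = 0.070d (to day 360) or 26/100 = 0.26d (to day 90).
- L = 21: 31.5d. Time average 31.5/381 = 0.083d or 31.5/111 = 0.28d.

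**Arm mean with some short follow-up.** The Interventions section allows 5 dropouts among 28 per arm. If all five stopped at day 90 (assumed), the wider excursion moves the arm mean by 23/28 × 0.070 + 5/28 × 0.26 = 0.10d up to 23/28 × 0.083 + 5/28 × 0.28 = 0.12d.

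**Simulation.** 5,000 runs, 23 per arm, day-0 origin, visit noise SD 1, between-patient SD 1 or 2 (assumed), no true treatment difference, and an excursion of 1 to 3 points at days 7 and 14 in both arms, observed only in the treated arm.
- All visits, AUC to day 360: false rejection about 4 to 6%.
- All visits, AUC to day 90: about 6 to 43%.
- Common visits only, either window: about 4 to 6%.

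**Time origin.** Table 1 does not define day 0 for controls. In the treated arm the stretch from Visit 1b to day 28 lasts 10 + 28 = 38 to 21 + 28 = 49 days. If control days were counted from Visit 1b (assumed), the same stretch would last 28 days there. Restricting the visits alone would then leave the first-segment weights unequal.

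**The case against.** Four points carry weight.

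First, dilution or illness following apheresis or infusion is not an artefact. Controls undergo neither procedure, the analysis is by randomised group, and the objective is to compare the therapy with standard care. A real early change therefore belongs to the effect of the allocated strategy. This stands. Bias needs a non-linear course that controls share but cannot show, and nothing in the protocol points to one.

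Second, both AUCs aim at the same area, at different resolution. Under a linear early course they coincide, and the stretch from day 0 to day 28 is 28/360 = 7.8% of follow-up. This also stands, and it keeps the point small. A reader might infer that the two AUCs measure different things, or that no AUC difference could be attributed to the macrophages. The documents do not support that.

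Third, a reader might take the day-90 figures as the expected size. A 3-point excursion gives 3 × 0.26 to 3 × 0.28, or about 0.8 points, but only for a participant whose follow-up ends at day 90. The planned window is one year, and the 6 to 43% false rejection comes from a 90-day AUC that the protocol does not plan.

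Fourth, the choice of visits for a secondary AUC is often left to a statistical analysis plan, and only a condensed article is at hand. That would answer a complaint about silence. It does not answer this one: the article states which scores enter the AUC, aims at comparable measurements, and offers a device that handles duration alone.

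**Conclusion.** The point holds as a cheap improvement to supportive analyses. The stated rule, applied to Table 1, puts the arms' MELD, UKELD, bilirubin, albumin, ALT and INR AUCs on different visit grids, and nothing in the plan corrects for that. For MELD, the distortion per point of an early excursion common to both arms is about 0.05 to 0.08 points on the one-year time average, with false rejection near the nominal 5% in the simulated cases. It is about 0.19 to 0.28 points per point only where follow-up ends near day 90. These figures rest on a trapezoidal AUC, an excursion resolved by day 28, and the reading of Table 1's intervals given above. The size of the excursion is assumed, since the protocol gives none. The primary result and the sample size are not in question.

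**What to change.** Add one sentence to the analysis plan: between-arm AUCs for MELD, UKELD, bilirubin, albumin, ALT and INR use only visits scheduled in both arms (Visit 1b as baseline, then Visits 3 to 7), with time counted from one origin defined the same way in both arms. Both halves are needed. In the working above, common visits give both arms the weights 14, 28, 31, 62, 135 and 90 days only when the origin is also common; a shared early excursion then adds nothing to the difference.

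Present Visits 2b, 2c and 2d descriptively within the macrophage arm, or keep the all-visit AUC as a labelled sensitivity analysis.

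No extra blood sample and no change to sample size is needed. The cost is that the treated arm's first two weeks after infusion no longer contribute to the test, so a genuine short-lived effect would appear only in the descriptive or sensitivity results.

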#### Secondary outcome measures

##### Transplant-free interval

The number of participants in each of the two treatment arms who are transplant free at 12 months will be expressed as proportions and a binomial test will be used for the comparison of proportions between the treatment arm and the control arm. The difference in proportions will be presented along with the 95% CI for the difference in the proportions.

The time to death or transplant will be presented using a Kaplan-Meier survival curve stratified by treatment and accompanied by a log-rank statistic comparing the two arms. Survival estimates with be presented by treatment arm at 3, 6, 9 and 12 months.

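### The rule that turns secondary outcomes into per-participant AUCs also covers transplant-free survival and the clinical event count, which it fits poorly, and the plots are planned by dose in a two-arm trial without dose groups.

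*Protocol article*

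**What the plan says.** The second paragraph of the Statistical analysis plan section covers the secondary outcomes. Among ELF, liver stiffness and blood parameters, its list contains "CLDQ score, transplant-free survival, number of clinical events, UKELD score". Changes in everything on the list "over the 1-year study period will be presented graphically by dose". The next sentence states that "these results will used to calculate an AUC for each participant and will be compared across the groups using a two-sample t-test", and continues "or non-parametric equivalent as appropriate". No outcome is excepted.

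The preceding paragraph, on MELD, adds: "In the event of varying durations in the trial follow-up, the average AUC per month will be used". The secondary-outcome sentence opens by likening itself to what went before, but does not say whether this averaging applies to it too.

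The Transplant-free interval section analyses the same outcome differently. The numbers "transplant free at 12 months will be expressed as proportions and a binomial test will be used for the comparison of proportions", with a 95% CI for the difference. In addition, "The time to death or transplant will be presented using a Kaplan-Meier survival curve stratified by treatment and accompanied by a log-rank statistic".

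Trial design and Allocation describe two arms randomised 1:1. Under Interventions, the active arm has one target, the largest number of cells obtainable up to 1×10^9, with a product minimum of 1.25×10^8. No dose groups are defined.

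**The concern.** An area under a curve summarises a quantity measured repeatedly in the same person. ELF, stiffness, CLDQ, UKELD and the blood results are of that kind. Transplant-free survival and a count of clinical events are not, and the article defines no serial score for either.

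Three things are at stake.

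- **Transplant-free survival** has up to three comparisons (binomial, log-rank, AUC), and nothing says which governs. In an open-label trial that leaves room to choose after the data are seen.
- **Clinical events** have no other stated analysis, yet fewer liver-related events is one of the secondary objectives in the Objectives section.
- **Plots by dose** do not show the randomised comparison. The achieved cell number is known only after randomisation, and controls have none.

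**Working it through.** **1. The plan's own figure.** Inputs from Sample size/power calculation: difference 1 SD, two-sided 5%, power 90%. The normal approximation gives n = 2 × (1.960 + 1.282)² / 1² = 21.0, rounded up to 22. With the noncentral t, power is 0.8997 at 22 and 0.912 at 23, so the stated 23 per group is reproduced. Adding 5 dropouts gives 23 + 5 = 28 per arm, as under Interventions. This calculation concerns MELD only and is not in dispute.

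**2. The outcomes against the rule.**

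| Outcome | Nature | Other stated analysis |
|---|---|---|
| ELF, stiffness, CLDQ, UKELD, bloods | serial score (Table 1) | none needed |
| Transplant-free survival | time to event | binomial, Kaplan-Meier, log-rank |
| Number of clinical events | count | none |

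**3. What an area would mean for transplant-free survival.** Let the indicator be 1 while alive without transplant and 0 afterwards. Its area to 12 months is min(T, 12), the restricted transplant-free time.

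- Death at month 3: area 3. Survivor: area 12. These differ, as they should.
- Divided by the participant's own follow-up, if that ends at death: 3/3 = 1 and 12/12 = 1. The event has disappeared.
- Divided by the full 12 months: 3/12 = 0.25 against 1.

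The result therefore depends on a convention that the article does not fix for this outcome.

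**4. What an area would mean for the event count.** Under a cumulative count, an event at month t adds 12 − t. One event at month 3 scores 9. Two events, at months 6 and 9, score 6 + 3 = 9. One event and two events tie, so the area does not measure the number of events.

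**5. Size, on assumed event rates.** The article gives no expected rate for the trial. Taking the Introduction's 4.4% one-year mortality in compensated disease as an illustration: expected events per arm 28 × 0.044 = 1.23; chance of none in one arm 0.956^28 = 0.28; chance of none in the trial 0.956^56 = 0.08.

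Simulation used 20,000 trials per scenario, 28 per arm, exponential event times and complete 12-month follow-up. It compared a t-test on restricted transplant-free time with log-rank at nominal 5%. Trials without events count as non-rejections.

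| Assumed control rate | Null: t-test | Null: log-rank | HR 0.5: t-test | HR 0.5: log-rank |
|---|---|---|---|---|
| 4.4% | 0.7% | 1.9% | 0.6% | 1.8% |
| 10% | 3.5% | 5.1% | 5.2% | 9.0% |
| 20% | 4.9% | 5.1% | 12.9% | 16.8% |

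**6. Why a replacement for clinical events must tolerate zeros.** Taking the Introduction's 5%–7% yearly decompensation as an assumed first-event rate: 28 × 0.05 = 1.4 to 28 × 0.07 = 1.96 expected per arm. The chance of none in one arm is 0.95^28 = 0.24 to 0.93^28 = 0.13. The chance that at least one arm has none is 1 − (1 − 0.24)² = 0.42 to 1 − (1 − 0.13)² = 0.24 (about 25% before rounding). In those trials a rate ratio from Poisson or negative binomial regression is zero, infinite or undefined.

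**7. Dose.** The permitted range in the active arm is 1×10^9 / 1.25×10^8 = 8-fold. This is what the article allows, not the spread expected. Three participants had more than one infusion.

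**The case against.** The strongest reply is that this is loose wording in a condensed article. Transplant-free survival has its own section with suitable methods, and a reader would naturally follow that specific text over a general sentence. This is fair, but nothing says that it governs, and it does not help clinical events.

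Several stronger readings are tempting and are not supported:

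- **That the plan is committed to t-tests.** It allows a non-parametric alternative. That changes the test but leaves the AUC step in place.
- **That no area, and so no estimand, exists.** Restricted transplant-free time and the area under a cumulative count can both be formed. With follow-up planned to day 360, most censoring would occur at a common time. The criticism is poor fit, and redundancy for transplant-free survival.
- **That false positives would rise.** In the simulation the t-test is conservative under the null. Log-rank power is also low, so neither method would be very informative.
- **That nearly all participants would share one value.** The rates are background figures for compensated cirrhosis. Entry at MELD 10–17 may bring more events, and the article does not define a clinical event.
- **That efficacy will be tested across dose groups, or that cell yield follows disease severity.** Dose is mentioned for graphs only, and the test sentence compares the groups. It may mean number of infusions. The article does not link yield to severity.

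**Conclusion.** The point holds as a mismatch between a stated rule and two of the outcomes it covers. For transplant-free survival, the AUC comparison duplicates and conflicts with the analyses under Transplant-free interval. It can also lose the event altogether, on the condition that per-month averaging carries over and follow-up ends at death. For clinical events, a poorly fitting method is the only one stated for a named secondary objective. The plots by dose do not correspond to any randomised grouping.

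The size is modest. At assumed 12-month control rates of 10% and 20% with a hazard ratio of 0.5, the t-test on restricted time loses about 4 percentage points of power against log-rank (5.2% against 9.0%, and 12.9% against 16.8%). These rates are assumptions. A reader might infer that the trial's main conclusion is at risk; it is not, since the primary MELD comparison and the sample size do not depend on this paragraph. The change is worth making because it removes a choice between analyses and costs almost nothing.

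**What to change.** 1. Take transplant-free survival and the number of clinical events out of the sentence on AUCs, leaving the serial scores.
2. State that transplant-free survival is analysed only as set out under Transplant-free interval.
3. Compare clinical events between the randomised arms as a count or rate over follow-up time, with a 95% CI. Use an exact or other method that still gives a result when an arm has few or no events. If one participant can contribute several events, the method should allow for that; a permutation comparison of the arm rates is one option.
4. Plot the secondary outcomes by randomised arm. Label any plot by achieved cell number or number of infusions as non-randomised and exploratory.

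The cost is a few lines in the analysis plan. Table 1 already records clinical events at every visit, and the planned Kaplan-Meier analysis already needs times of death and transplant. The article does not say whether dates of other clinical events are collected. A count over follow-up time does not need them, provided that the start and end of each participant's follow-up are known.
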